***Cost-utility analysis***

The health economic analysis will determine the cost-utility of screening patients for anxiety and depression in OA compared with a standard consultation without screening. A cost-consequence analysis will initially be reported, describing all the important results relating to costs and consequences. Subsequently, an incremental cost-utility analysis will also be undertaken using patient responses to the EQ-5D questionnaire, to calculate the cost per additional QALY gained. The base case cost analysis will adopt a National Health Service (NHS) and personal social services (PSS) perspective [64]. A broader costing perspective will be considered in a sensitivity analysis, taking into account NHS/PSS costs, patients’ personal expenditure and costs associated with work loss. The data for costs is likely to have a skewed distribution therefore the plan is to explore the nature of the distribution of costs. If the data is not normally distributed, the non parametric comparison of means (e.g. bootstrapping) will be undertaken. Where differences in baseline characteristics occur between trial arms, for example in baseline EQ-5D score, the analysis will control for these baseline differences using regression-based adjustment. Efforts will be made to minimise the problem of missing data, but if this does pose a problem at the analysis stage then multiple imputation techniques will be used. The robustness of the results will be explored using sensitivity analysis. This will explore uncertainties in the trial based data itself, the methods employed to analyse the data and the generalisability of the results to other settings. Uncertainty in the confidence to be placed on the results of the economic analysis will be explored by estimating cost effectiveness acceptability curves. These plot the probability that the intervention is cost effective against threshold values for cost effectiveness.

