## Secondary objective

A secondary objective of the trial will be to evaluate the cost utility of screening for depressive and anxiety symptoms in patients with OA.

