Costs: Health sector costs will include primary and secondary care contacts, investigations, medication and contacts with other health care professionals such as physiotherapists and community psychiatric nurses. Primary health care resource use (GP and practice nurse consultations/home visits) and medications will be collected from a review of primary care medical records, covering the full 12 month follow-up period for all study participants. Information on secondary care attendances and patient borne costs will be gathered using the postal self-report questionnaires. Questions on patients’ personal expenditure will concentrate on private health care use and over-the-counter treatments. Productivity costs will be calculated using data collected on occupation and days off work due to illness. Unit costs will be obtained from standard sources and health care providers. Due to the nature of the study, generic health care resource use will be collected (i.e. not specific to the treatment of OA). Information on resource use from the self-report questionnaires will be collected at 6 months and 12 months, with each questionnaire covering a 6 month recall period.

Quality of life measures: All patients will be asked to complete the 5-level version of the EuroQoL-5D (EQ-5D) [55] questionnaire at baseline, 3 months, 6 month and 12 months in order that quality-adjusted life years (QALYs) over the 12 month time period can be calculated for each study participant. The QALYs combine information on health-related quality of life and survival. The SF-12 will also be included as a measure of generic health-related quality of life, thus allowing an alternative method of calculating QALYs using the SF-6D in a sensitivity analysis.

The conceptual domains, operational definitions and empirical measures of each of the items included in the postal questionnaires are detailed in Table 2. This table also highlights in which of the questionnaires (baseline, 3, 6 or 12 months) the item is included.

**Table 2:** Summary of full postal questionnaire content

| **Conceptual domain** | **Operational definition** | **Empirical measure** | **Number of items** | **Time** |
| --- | --- | --- | --- | --- |
| **Primary Outcomes** |  |  |  |  |
| Pain intensity | Current intensity of the index pain | NRS 0-10 * | 1 | B, 3FU, 6FU, 12FU |
| **Secondary Outcomes** | |  |  |  |

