# *Statistical analysis*

Both the primary and secondary analysis will be by intention to treat and appropriate multiple imputation techniques will be used to account for missing data. The primary outcome, the current pain intensity component (0-10 numerical rating scale) of the Chronic Pain Grade [48], will be treated as interval in nature. Multilevel linear mixed modelling will be used to account for the clustered nature of the data. Using treatment by group interaction terms, differences in the mean response profiles will be investigated and quantified using appropriate 95% confidence intervals for the differences between intercept and gradient estimates.

Standard goodness of fit tests will be applied and if the distribution of the residuals is markedly non-normal, bootstrapping will be considered. Time varying covariates can also be accommodated within the multilevel framework.

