The back page of the questionnaire explains that we may wish to contact the GP to discuss some of their responses further and asks the GP to provide their name and contact details. When a questionnaire is returned to the centre the information will be entered into a database and at that stage a study number will be assigned to the questionnaire. The back page of the questionnaire will be removed from the questionnaire and stored separately in a locked filing cabinet in the administration department of this Research Centre. The information given in the questionnaire will be useful to us regardless of whether contact information is provided; however, having contact information for some GPs will help us to target our sampling for qualitative interviews (as outlined below). For those GP participants who later take part in a semi-structured interview, their questionnaire responses will be used to inform that interview.

**Analysis:** Simple descriptive characteristics.

**Table 6:** Content of GP’s experience of participating in POST questionnaire

| **Item Number** | **Item Description** | **Item response** |
| --- | --- | --- |
| 1 | Impact on consultation time | 5 point Likert scale |
| 2 | Amount of additional time | 7 options plus free text option if appropriate |
| 3 | Impact on doctor-patient communication | 5 point Likert scale plus additional 4 point Likert scale where there was a impact |
| 4 | Effect on patient management | 5 point Likert scale |
| 5 | Reasons for excluding patients | free text |
| 6 | Ease of incorporating screening questions | 4 point Likert scale |
| 7 | Additional comments | Free text |
|  | Name |  |
|  | Contact details |  |

1. **Semi-structured GP interviews**

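### The cost-utility plan makes baseline EQ-5D adjustment depend on observed differences, does not say how practice clustering enters, and names no intervention delivery cost

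*Protocol*

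**What the plan says.** Cost utility is the trial's named secondary objective: "A secondary objective of the trial will be to evaluate the cost utility of screening" (Protocol, Secondary objective). Three parts of the plan bear on it.

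**Baseline adjustment.** The Cost-utility analysis section says: "Where differences in baseline characteristics occur between trial arms, for example in baseline EQ-5D score, the analysis will control for these baseline differences", by regression. It gives no rule for deciding that a difference has occurred.

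**Comparison of costs.** The same section says: "If the data is not normally distributed, the non parametric comparison of means (e.g. bootstrapping) will be undertaken". It goes on to missing data, sensitivity analyses and acceptability curves. Practice, cluster and resampling unit do not appear. Clustering is dealt with in the preceding section, Statistical analysis: "Multilevel linear mixed modelling will be used to account for the clustered nature of the data". That sentence comes directly after the one on the pain outcome, although the section opens more broadly: "Both the primary and secondary analysis will be by intention to treat".

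**Cost items.** Under Data collection, health economics outcomes: "Health sector costs will include primary and secondary care contacts, investigations, medication and contacts with other health care professionals". The perspective is set later: "The base case cost analysis will adopt a National Health Service (NHS) and personal social services (PSS) perspective". Neither place names the cost of delivering the intervention. The GP questionnaire (Table 6, item 2) does ask about "Amount of additional time", but its planned analysis is descriptive only.

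**The concern.** Whether to adjust for baseline EQ-5D is a choice that can move the QALY difference, and here it is left until the arms have been compared. Two analysts could follow the text faithfully and report different estimates. Only about 44 practices are randomised, and patients consent after randomisation. The protocol itself regards selection and recruitment bias as a serious threat in this design, so some baseline difference is likely.

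Practices are the randomised unit. A bootstrap or regression that took patients as independent would give intervals that are too narrow and acceptability curves that are too steep. The text permits a method that respects practices but does not require one.

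The comparison is of a systems intervention with usual care. If its delivery is not costed, the incremental cost is understated, and the error runs in favour of screening.

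**Working it through.** **1. The protocol's own figures.** Inputs from Sample size: autocorrelation 0.5, three repeated measures, effect 0.2 SD, alpha 0.05 (two-sided), power 90%, ICC 0.03, cluster size 30, non-response 25%.

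- Per arm: 2(1.960 + 1.282)² × {1 + 2 × 0.5} / (3 × 0.2²) = 350.2 (stated 350).
- Design effect: 1 + 29 × 0.03 = 1.87.
- Total: 2 × 350 × 1.87 = 1309 (stated 1309).
- Practices: 1309 / 30 = 43.6 (stated 44).
- To contact: 1309 / 0.75 = 1745.3 (stated 1745).

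All reproduce. The ICC of 0.03 is for pain; the protocol gives none for costs or QALYs.

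**2. If clustering were ignored in the economic analysis.** Naive SE / correct SE = 1/√DE. Coverage of a nominal 95% interval = 2Φ(1.96/√DE) − 1. Cluster size is 30 throughout, and every ICC below is an assumption for costs and QALYs.

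| ICC | Design effect | Naive/correct SE | Coverage |
| --- | --- | --- | --- |
| 0.01 | 1.29 | 0.880 | 91.6% |
| 0.03 | 1.87 | 0.731 | 84.8% |
| 0.05 | 2.45 | 0.639 | 78.9% |

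At 0.03 the standard error is 1 − 0.731 = 27% too small. On an acceptability curve, under a normal approximation, a probability of 0.80 with the correct standard error would appear as Φ(0.842 × √1.87) = 0.875.

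**3. How baseline EQ-5D enters the QALY.** Assume QALYs are the trapezoidal area over 0, 3, 6 and 12 months, the times at which EQ-5D is collected. The baseline value then has weight 0.25/2 = 1/8. An assumed chance difference of 0.02 shifts the QALY difference by 0.02/8 = 0.0025 through the baseline point alone, and by 0.02 if the difference persists in full at every time point. No EQ-5D values are given, so this shows only the mechanism.

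**4. What the cost sources can show.** Primary care use comes from record review, which counts consultations, prescriptions and referrals (Table 5). The index consultation occurs once in each arm, so a count cannot show that five questions, and any response to a positive screen, took longer than one question. Under Post-randomisation, the facilitator meeting, template demonstration and crib sheet occur in both arms; the guideline presentation and four papers are for intervention practices only. The incremental delivery items are therefore the extra consultation time, the presentation and the papers. The protocol gives no unit costs or durations, so their size cannot be computed.

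**The case against.** A reader might infer that the protocol plans an ordinary patient-level bootstrap, costs screening at zero, and will therefore report a biased and over-precise result. The text does not support that.

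- **Clustering.** No resampling unit is named, and both bootstrapping and regression can be done with practice as the unit. The Statistical analysis section opens by referring to primary and secondary analysis, and cost utility is a secondary objective. Resampling detail may also be left to an analysis plan not shown here. This stands against any claim that clustering will be ignored. It does not show that clustering is covered: the multilevel sentence follows the pain outcome, and the Cost-utility analysis section sets its own rules, including a conditional rule for imputation where Statistical analysis states that imputation will be used. It therefore reads as self-contained.
- **Delivery cost.** The cost list is worded as open, nothing is excluded, and part of the facilitator's work is common to both arms. All of this stands. What remains is that no incremental delivery item is named and the one relevant measurement is not linked to costing.
- **Baseline adjustment.** With randomised practices, leaving out adjustment mainly loses precision and leaves chance imbalance, so bias does not follow automatically. The baseline EQ-5D is also collected by post after the consultation that delivers the intervention, so adjusting for it could remove part of an early effect. That caveat is sound, but it applies equally to the protocol's conditional adjustment and does not justify a data-dependent trigger.

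**Conclusion.** The point holds in three parts of unequal strength.

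The baseline rule is the firmest. It is stated rather than left open, it depends on the observed data, and it has no criterion.

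The clustering part is a gap in specification. Its size is conditional: standard errors about 27% too small and coverage about 85% arise only if practices were ignored and the pain ICC also applied to costs and QALYs. Over assumed ICCs of 0.01 to 0.05, coverage runs from 92% to 79%.

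The delivery-cost part is an item left unnamed in an open list. If the incremental items were omitted, the direction would favour screening; the amount cannot be derived from the protocol.

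The documents do not establish that the cost-effectiveness result is biased or too precise. They leave room for it to be, on the trial's secondary objective, and a few sentences would close that room.

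**What to change.** - Adjust QALYs for baseline EQ-5D by regression in all cases, whatever the observed difference. Because the baseline questionnaire follows the index consultation, report an unadjusted sensitivity analysis beside it.
- State that the cost and QALY comparison and the acceptability curves will use either a two-stage bootstrap (practices, then patients within practices) or a multilevel model with practice as a random effect.
- Name the incremental delivery costs: extra index-consultation time, using Table 6 item 2, and the intervention-only guideline presentation and papers. Leave out what both arms receive. Item 2 is GP-reported and asked in both arms, so the relevant quantity is the difference between arms, with a sensitivity range.

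The cost is some wording in the health-economics plan and a little programming. No new patients or patient questionnaires are needed. The downside is wider intervals and a slightly less favourable cost per QALY.

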***Run-in period***

An internal pilot of the trial protocol will take place in four practices, two in each arm. This “run-in” period will be used to ensure that our methods and key assumptions outlined in this protocol work successfully and that the day-to-day administration of the trial runs smoothly. Particular attention will be paid to the recruitment of GP practices, completion rate of the screening template, response rate to, and completion rate of the baseline postal questionnaire and the consent rate to further contact and medical record review. This phase of the trial will run until recruitment at these four practices is complete, which we anticipate to take three months. The template will not be activated in any further practices until this run-in period is complete. Data collected during this phase of the trial will be included in final data analysis as no interim analysis will be carried out with this data. Data from this phase of the trial will only be excluded from the final analysis if any substantial amendments to the current protocol have to be made.

**Timescale**

The timing of the study milestones is illustrated in Figure 3.

# Closing remarks

The implementation of this cluster randomised trial will allow us to investigate the effect of prompting GPs to ask about concurrent anxiety and depressive symptoms during a peripheral joint pain/OA consultation screening. A previous observational study within our centre has demonstrated the feasibility of GPs carrying out depression screening in the OA consultation and shown our ability to subsequently recruit and follow-up patients [23]. The run-in period at the beginning of the trial with four GP practices will allow us to test our assumptions and processes before moving on to the main trial.

**Amendment to POST Study Protocol_V2.0_24.5.11:**

**A nested substudy of general practitioners’ experiences of participating in POST**

This component of the trial is intended to explore individual GP’s experience of participating in the POST study. The objective of this component is to identify barriers and facilitators related to screening OA/joint pain patients in both arms of the trial and to explore the experience and perceived value of including questions about anxiety and depressive symptoms. It will also explore how GPs have engaged with the trial and in the use of the screening template during their consultations, and whether there are differences between the two arms of the trial. There will be two methods used to explore GP’s experience of participating in POST, firstly a brief questionnaire that will be distributed to all GPs at participating GP practices, and secondly, a semi-structured interview with a sub-group of participating GPs. Both of these methods are outlined below.

1. **GP questionnaire**

**Study participants:** All general practitioners at the general practices taking part in POST

**Method:** Post-intervention self-complete questionnaire. This is a brief 7 item questionnaire (Table 6) that will gather information on the GPs opinions on participating in POST. A similar questionnaire was used to gather feedback from GPs involved in a previous research study that involved the use of a screening template. The same questionnaire will be completed by GPs in both arms of the trial. All information and instructions are included in the questionnaire. As part of their participation in the trial GPs are made aware that we will ask them for feedback at the end of their study period and therefore a separate GP information leaflet and cover letter is not required. The questionnaires will not be addressed to specific GPs, instead copies of the questionnaire will be given to the Practice Manager at the end of the GP practice’s study period (approximately 3 months) and he/she will ask the GPs at their practice to complete the questionnaire. Completed questionnaires will be returned via the Practice Manager to this Research Centre in the stamped address envelope provided.

The back page of the questionnaire explains that we may wish to contact the GP to discuss some of their responses further and asks the GP to provide their name and contact details. When a questionnaire is returned to the centre the information will be entered into a database and at that stage a study number will be assigned to the questionnaire. The back page of the questionnaire will be removed from the questionnaire and stored separately in a locked filing cabinet in the administration department of this Research Centre. The information given in the questionnaire will be useful to us regardless of whether contact information is provided; however, having contact information for some GPs will help us to target our sampling for qualitative interviews (as outlined below). For those GP participants who later take part in a semi-structured interview, their questionnaire responses will be used to inform that interview.

**Analysis:** Simple descriptive characteristics.

**Table 6:** Content of GP’s experience of participating in POST questionnaire

| **Item Number** | **Item Description** | **Item response** |
| --- | --- | --- |
| 1 | Impact on consultation time | 5 point Likert scale |
| 2 | Amount of additional time | 7 options plus free text option if appropriate |
| 3 | Impact on doctor-patient communication | 5 point Likert scale plus additional 4 point Likert scale where there was a impact |
| 4 | Effect on patient management | 5 point Likert scale |
| 5 | Reasons for excluding patients | free text |
| 6 | Ease of incorporating screening questions | 4 point Likert scale |
| 7 | Additional comments | Free text |
|  | Name |  |
|  | Contact details |  |

1. **Semi-structured GP interviews**

This component of the study involves semi-structured interviews with a sub-group of participating GPs. This interview schedule, which is based around the work of Coventry et al (2011) for screening for depressive symptoms in primary care patients with a long term health problem [65], is designed to complement the GP questionnaire, the responses to which will also contribute to the basis of the interview. GPs in the control arm were not asked to screen for depressive and anxiety symptoms, and therefore questions relating to the impact of screening for these symptoms on consultation time, doctor-patient communication and GP engagement will be limited to GPs in the intervention arm of the trial. However, those in the control arm will be asked their general views on the frequency and degree of presentation of such symptoms amongst their patients. In addition, both arms asked the question regarding pain intensity and so questions regarding the impact that this had will be included in the interview schedule for both arms. GPs from both arms of the trial will also be asked about the acceptability of screening in general for OA/joint pain patients and in how they have engaged with the study. The interview schedules are considered as topic guides for the interviews.

**Study participants:** It is anticipated that up to 40 interviews may be conducted, 20 from each arm. However, interviewing will continue until saturation is reached, i.e. no new themes are emerging from the process of on-going analysis. GPs will be sampled from those who have given their contact details in the GP questionnaire, ideally these will include GPs from practices that have screened the target number of patients, exceeded their screening target and screened less than target.

**Method:** Semi-structured interviews (based on the interview schedules (summarised in Table 7)), estimated to last for approximately 30 minutes, will be conducted with GPs who have consented to take part. Those GPs who have provided their contact details in the questionnaire will be provided with an information letter. There are two versions of this letter, one for GPs in each of the trial arms. The letter contains all the information necessary to make an informed decision on whether to continue to participate. A follow-up telephone call will be made in order to see if GPs are indeed happy to take part and to arrange a convenient time for the interview to take place. Informed consent will be taken at the time of the interview by the trained interviewer and all interviews will be audio recorded.

**Analysis:** The audio recordings will be fully transcribed in an anonymised format. Content analysis will be performed with the specific focus on the research questions as outlined in the interview schedule. As codes emerge, data will be checked for additional confirmatory or challenging evidence within and between individual interviews, and across the two groups in line with basic principles of qualitative data analysis [66]. Where possible, data from the questionnaires will be combined those from the interviews in line with a mixed methods approach [67].

**Ethics:** Anonymity is the principal ethical challenge. To address this, participants will be given a unique ID number and pseudonym. Identifiable names of people, places or institutions will be removed from each transcript. Digital recordings will be held on a dedicated secure University server, and will only be accessible to those directly involved in the study. All quotations in reports, publications, and presentations will be presented in an anonymous format.

**Table 7:** Outline of interview schedule for GPs

| **Domains** | **Intervention arm (yes/no)** | **Control arm (yes/no)** |
| --- | --- | --- |
| General patient population including psychological problems | Yes | Yes |
| Views of psychological problems in joint pain/OA | Yes | Yes |
| Presentation and detection of psychological symptoms | Yes | Yes |
| Management | Yes | Yes |
| Communication | Yes | Yes |
| Training and development | Yes | Yes |
| Taking part in POST | Yes | Yes |
| Follow-up | Yes | Yes |
| GP practice | Yes | Yes |
| Ease of asking questions | Yes | No |
| Differences between GAD & PHQ | Yes | No |
| Usefulness of screening template | Yes | No |
| Patients included/excluded | Yes | No |

